### Time period

1 January 2016 to 30 September 2023, with infants grouped by date of birth into three groups according to date of implementation of the care bundle: pre-implementation period—1 January 2016 to 31 August 2022; implementation period—1 September 2022 to 31 December 2022; evaluation period—1 January 2023 to 30 September 2023, followed up for 3 months (until 31 December 2023) to cover the full neonatal stay of the final participant.

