#### Secondary outcomes

Exclusive feeding with own mother’s milk at discharge.Any NEC, including NEC not requiring surgery and not resulting in death.

### Data analysis strategy: workstream 1

After data cleaning, the number of infants with missing data across key variables will be tabulated and the total number of exclusions and final study population size determined. Descriptive statistics will be presented to summarise the distribution of baseline variables during each of the three study phases, separately for the EMNODN units (intervention group) and all other units in England and Wales (control group). Continuous variables will be reported with means and SDs, if shown to be normally distributed using a combined skewness and kurtosis test, or otherwise will be reported using medians and IQRs. Categorical variables will be reported with frequencies and percentages. P values for differences between the three time periods will be reported using the χ^2^ test or the Wilcoxon rank-sum test, as appropriate.

We will use ITS analysis to assess the impact of implementation of the care bundle on the outcomes listed above, as has been used previously in neonatal research.^27^ This is a strong quasiexperimental design which accounts for underlying trends in an outcome. If, for example, rates of NEC were already in decline prior to the implementation of the bundle, the ITS methodology will detect any additional impact of the bundle, above the background decline. It can also account for the impact of any other interventions or changes in population characteristics which might themselves impact outcomes.

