We will aggregate outcomes by month of birth (or by 2-month period if necessary to improve statistical power, without detriment to interpretation of results) and plot time series graphs to show the number of cases of each outcome per month over the study period in the EMNODN units combined. We will use a quasi-Poisson generalised additive mixed model^28^ to estimate an incidence rate ratio (IRR) for changes in the incidence of the outcomes in EMNODN units during the evaluation phase, relative to the pre-implementation period. Data for the 4-month implementation phase will be plotted graphically but excluded from statistical modelling as this period is too short to be able to model changes in incidence compared with the pre-implementation period. We will similarly plot and model data for infants admitted to units in the control group, to assess whether there are any changes in the IRR to exclude confounding due to other events or interventions which occurred around the time that the care bundle was introduced.

We will incorporate several covariates into our models as follows:

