ITS studies are not usually affected by confounders relating to population characteristics as these do not typically change significantly over time.^33^ If the characteristics of infants born during each of the three study time periods differ, we will include covariates to capture any differences in potential confounders by month of birth, such as: median GA; percentage of male admissions; median birth weight; percentage of infants with a high-risk NMR-2000 score (a validated score of in-hospital mortality risk)^34^; percentage of infants with a major congenital anomaly; and median length of stay.Plots of the autocorrelation function and partial autocorrelation function will be examined to identify plausible values of the autoregressive (AR) and/or moving average (MA) terms to capture autocorrelation between data points. We will use the AIC to compare models with different plausible values of AR and MA terms, with a smaller AIC indicating better model fit.

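### Case-mix adjustment of the primary ITS models is conditional on an undefined difference between periods, drawn from an open list that includes a post-birth variable

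*Protocol article*

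**What the plan says.** Under Data analysis strategy: workstream 1, the ITS models always carry an admissions offset, a secular trend, a step, a change in slope, a seasonal spline and a lockdown indicator. Infant characteristics are treated differently. The stated premise is that "ITS studies are not usually affected by confounders relating to population characteristics as these do not typically change significantly over time", and the rule that follows is "If the characteristics of infants born during each of the three study time periods differ, we will include covariates". The purpose and candidates are given as "to capture any differences in potential confounders by month of birth, such as: median GA; percentage of male admissions; median birth weight", followed by the NMR-2000 high-risk percentage, the major congenital anomaly percentage "and median length of stay".

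The text does not say what counts as a difference, or whether all listed covariates enter or only those that differ.

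The one between-period comparison described is in the descriptive paragraph of the same section: "P values for differences between the three time periods will be reported". Those tables are produced separately for EMNODN and control units. The article does not say that these p values decide the adjustment.

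Confounder adjustment without a condition is stated only under Secondary analyses, for the before-after logistic regression.

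**The concern.** This is a rule that the article states, not a detail it omits. As written, the covariate set of the model for each primary outcome depends on what the data show, through a judgement that two careful analysts could make differently.

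Three features make the rule weak for this design:

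- **It compares period averages.** An ITS step is confounded by a departure from trend at the interruption. A slow drift can separate the period averages yet be largely absorbed by the trend term. An abrupt change in the short evaluation period can matter and not be noticed.
- **It counts all three periods.** The implementation phase is one of them, although "Data for the 4-month implementation phase will be plotted graphically but excluded from statistical modelling".
- **Length of stay is not fixed at birth.** Death from NEC ends the stay, and the bundle itself may alter it. Adjusting for it could remove part of the effect or introduce bias.

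What is at stake is mainly the EMNODN–control comparison. The control series is there to rule out concurrent causes, which works best if both series are adjusted in the same way.

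**Working it through.** The article gives no figure for this rule, so there is nothing to reproduce. The check asks how a p-value trigger would behave, if one were used.

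**Inputs from the article**
- Pre-implementation, "1 January 2016 to 31 August 2022": 80 months. Implementation: 4 months. Evaluation, "evaluation period—1 January 2023 to 30 September 2023": 9 months. Modelled months: 80 + 9 = 89.
- EMNODN infants per month, from Sample size calculation: 23/0.55 = 41.8 (reading 23 as infants receiving own mother's milk) and 3/0.07 = 42.9. The Introduction's 476 infants in 2022 give 476/12 = 39.7. Use 42.
- Period sizes: 80 × 42 = 3,360; 4 × 42 = 168; 9 × 42 = 378; total 3,906.

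**Assumptions**
- Three-period chi-squared test at two-sided 5%.
- High-risk share of 20%, changing only in the evaluation period.
- Control group ten times the size of EMNODN (the Introduction counts 11 English networks, and the control group adds Wales).

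**Chance that the shift is flagged in EMNODN.** The noncentrality is λ = Σ nᵢ(pᵢ − p̄)² / [p̄(1 − p̄)], on 2 df, with critical value 5.99.
- 20% to 23%: p̄ = (3,528 × 0.20 + 378 × 0.23)/3,906 = 0.2029. λ = (3,528 × 0.0029² + 378 × 0.0271²)/(0.2029 × 0.7971) = 1.90. Power 0.22.
- 20% to 25%: λ = 5.24. Power 0.52.
- 20% to 27%: λ = 10.2. Power 0.82.
- Other assumed shares: 10% to 13%, 0.35; 54% to 58%, 0.25; 54% to 60%, 0.50.

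**Same shift in the control group.** λ scales with size. At ten times, 20% to 23% gives λ = 19.0 and power 0.98; 20% to 25% gives λ = 52.4 and power above 0.99. If the control group were only five times larger, 20% to 23% would be flagged with probability 0.79.

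**Chance that control is adjusted and EMNODN is not.** The infants are different, so the probabilities multiply: 0.98 × (1 − 0.22) = 0.76 for 23%, and about 1 × (1 − 0.52) = 0.48 for 25%.

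**Effect on the estimate.** A simulation used 1,000 runs per scenario, a quasi-Poisson step-and-trend model, a true bundle IRR of 1, and a high-risk share rising from 20% to 25% at evaluation. The risk ratios for high-risk infants are assumed.

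| Outcome | Never adjust | Conditional | Always adjust |
|---|---|---|---|
| Own mother's milk (55%, RR 0.6): mean IRR | 0.982 | 0.997 | 1.003 |
| Rejection rate | 0.059 | 0.049 | 0.049 |
| NEC (7%, RR 4): mean IRR | 1.082 | 1.014 | 0.987 |
| Rejection rate | 0.066 | 0.049 | 0.036 |

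Conditional relative to always: 0.997/1.003 = 0.994 for milk and 1.014/0.987 = 1.027 for NEC, a gap of about 1% to 3%.

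**Drift without a step.** A smooth rise from 20% to 25% over the 93 months is flagged with probability 0.20, although the trend term largely absorbs it.

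**The case against.** Much of the case on the other side stands.

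- **The trigger is not stated.** The p values are announced as descriptive reporting, and the covariate rule names no test or threshold. A reader might infer that the plan judges differences by significance, but the text does not say so. The flag probabilities apply only under that reading. A definition may also exist in a full protocol or analysis plan. That would answer the missing criterion, but not the conditional rule or the inclusion of length of stay.
- **Error rates hold up.** A reader might infer that data-dependent selection spoils the type I error or interval coverage. In the simulation the conditional rule rejected at 0.049 for both outcomes, and for NEC its mean IRR was about as far from 1 as that of always adjusting.
- **False flags are not the harm.** With six independent 5% tests and no true differences, at least one fires with probability 1 − 0.95⁶ = 0.26. A false flag merely adds covariates that the remedy would add anyway.
- **Bias is small beside the noise.** About 3 NEC cases per month means about 27 in evaluation and 240 before. Even without a trend term, SE(log IRR) is about √(1/27 + 1/240) = 0.20. The 1.082 from never adjusting is ln 1.082 = 0.079, or about 0.4 SE.
- **Different models for the two groups are possible, not planned.** Control data are to be modelled similarly, and nothing says that the trigger runs group by group. Only the descriptive tables are separate.
- **There is a safety net.** The secondary logistic regression adjusts every primary and secondary outcome for infant, maternal and unit factors, with no trigger, and examines effect modification by group. It would be wrong to say that case-mix imbalance goes unexamined.

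None of this supplies a criterion, closes the list, or makes length of stay a birth-time variable.

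**Conclusion.** The point holds in a limited form. The adjustment set of the primary ITS models is not fixed in advance. It depends on an undefined difference between periods, draws on an open list, and may include a variable measured after birth.

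The expected numerical damage is small: about 1–3% in the IRR on average, with type I error near nominal, in the scenarios simulated. The harm is a primary estimate open to analyst discretion and, if separate p values serve as the trigger, possible asymmetry with the control series. Under that inference, a shift to 23–25% would be flagged about 22–52% of the time in EMNODN and nearly always in control.

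These figures rest on the assumed 20% share, 5% test level and tenfold control group, and on the derived 42 infants per month. The documents do not support a claim of invalid inference, or one that the two series will in fact be adjusted differently. The point is worth correcting because correction is cheap.

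**What to change.** Replace the conditional sentence with a fixed rule:

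- Name one closed set of birth-time covariates from those already listed: median gestational age, median birth weight, percentage male, percentage with a high-risk NMR-2000 score, and percentage with a major congenital anomaly.
- Include the same set in every ITS model, EMNODN and control, whatever the observed differences.
- Remove median length of stay.
- Report the model without these covariates alongside.
- Keep the between-period p values, if wanted, as description only.

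The plan already intends to use all five variables, so the change is one of wording. It costs about five degrees of freedom out of 89 modelled months. In simulation the SD of the log IRR for NEC was about 0.23 to 0.24 under every strategy, so the loss of precision is negligible. If outcomes are pooled into two-month periods, as the plan allows, there would be only about 89/2 ≈ 44 points. The cost would then be relatively larger, and precision there was not checked.

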### Intervention

The NEC care bundle, designed by a multidisciplinary team, consists of recommendations for neonatal units, alongside parent-facing information, to promote own mother’s milk feeding and ensure optimum nutritional care of preterm infants. A schematic representation of the care bundle is shown in figure 1, giving an overview of an infant’s journey through neonatal care and opportunities to reduce the risk of NEC.

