**Figure 1 F1:**
[figure not shown]
Overview of the East Midlands Neonatal Operational Delivery Network (EMNODN) necrotising enterocolitis (NEC) care bundle.

Recommendations to optimise nutritional care include guidance on: ensuring early and adequate parenteral nutrition given when infants cannot have sufficient milk feeds such as in the first hours after birth, while building milk feeds and when unwell (following established National Institute for Health and Care Excellence guidelines^20^); use of oropharyngeal colostrum^21^ (the practice of giving own mothers’ first milk directly into the infant’s oropharynx to enhance immunity and protect against NEC); optimal time and speed of increasing milk feeds^22^; and use of other interventions such as human donor milk,^23^ probiotics^24^ and breastmilk fortifiers.^25^

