#### Primary outcomes

Receiving any own mother’s milk at discharge (exclusively or in combination with infant formula).Receiving any own mother’s milk on day 14 of life (exclusively or in combination with infant formula).Severe NEC requiring surgery or resulting in death.^26^

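### Median length of stay is listed as a possible confounder for the interrupted time series model, although it is settled only after the bundle has acted and can be changed by the bundle, by feeding and by NEC

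*Protocol article*

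**What the plan says.** The covariate list in the protocol article, under Data analysis strategy: workstream 1, first argues that population characteristics seldom confound an ITS study. It then makes an exception: "If the characteristics of infants born during each of the three study time periods differ, we will include covariates to capture any differences". These covariates are to be monthly summaries of possible confounders. The examples are median gestational age, percentage male, median birth weight, percentage with a high-risk NMR-2000 score, "percentage of infants with a major congenital anomaly; and median length of stay".

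Three other parts of the article bear on this:

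- **Intervention.** The bundle is designed "to promote own mother’s milk feeding and ensure optimum nutritional care of preterm infants". The text with Figure 1 includes guidance on "optimal time and speed of increasing milk feeds", along with parenteral nutrition, donor milk, probiotics and fortifiers. These act during the stay.
- **Primary outcomes.** These are any own mother's milk at discharge, any own mother's milk on day 14, and "Severe NEC requiring surgery or resulting in death".
- **Modelling.** The IRR contrasts the evaluation period with the pre-implementation period. The four-month implementation period is plotted but left out of the model.

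The article gives no reason for treating length of stay as a confounder. It does not confine it to a sensitivity analysis or say that an estimate without it will be shown.

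**The concern.** A confounder has to precede the exposure or at least be unaffected by it. Gestational age, sex, birth weight and congenital anomaly meet that test because they are fixed at birth. Length of stay does not, since it is known only when the infant goes home or dies. Adjusting for it holds constant something the bundle may have changed, and something the outcomes themselves may have changed.

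The ITS model is the main analysis for all three primary outcomes. The question it is meant to answer is the total effect of introducing the bundle. An IRR conditional on length of stay answers a different question and could be read as the total effect.

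**Working it through.** **Timing of length of stay against each primary outcome**

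| Primary outcome | When it is determined | Relation to length of stay |
|---|---|---|
| Own mother's milk at discharge | At discharge | Stay ends at the same moment; stay may lie partly on the path from bundle to outcome |
| Own mother's milk on day 14 | Day 14 | For an infant still admitted, stay is completed later; it cannot be a cause, but may be a consequence |
| Severe NEC | During the stay | Death ends the stay and surgery may prolong it; stay is partly a consequence of the outcome |

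In none of the three rows is length of stay a baseline variable. That follows from the article's outcome definitions. That the bundle changes stay is an inference from its content; the article does not say so.

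**Direction**

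Let β be the model coefficient per day of monthly median stay, and Δ the change in stay that comes with the bundle. Approximately:

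adjusted log IRR = total log IRR − β × Δ

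Assume longer stay goes with less own mother's milk (β < 0) and more NEC (β > 0). If the bundle shortens stay (Δ < 0), both estimates move toward the null. If it lengthens stay (Δ > 0), both move away from it.

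**Size, on assumed inputs**

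The article has no length-of-stay figures, so this is an illustration only.

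- From the article: 80 pre-implementation and 9 evaluation months (80 + 4 + 9 = 93, as stated). About 42 infants per month (23 / 0.55 = 41.8; 3 / 0.07 = 42.9). True effects of +15 points for own mother's milk and a two-thirds reduction in NEC, as in the sample size section.
- Assumed: illness severity adds 12 days per SD, lowers own mother's milk and raises NEC. NEC adds 30 days. Own mother's milk removes 4 days. The direct bundle effect on stay is 0, −7 or +7 days.
- Model: Poisson with offset, trend, step and seasonal terms, fitted with and without monthly median stay; 500 simulated data sets. There was no lockdown term, slope change or autocorrelation.

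| Assumed direct bundle effect on stay | Total change in median stay (days) | Own mother's milk IRR, without → with stay | NEC IRR, without → with stay |
|---|---|---|---|
| None (only via feeding and NEC) | −1.3 | 1.296 → 1.272 | 0.313 → 0.331 |
| −7 days | −8.2 | 1.295 → 1.160 | 0.317 → 0.440 |
| −7 days, severity unrelated to own mother's milk | −8.4 | 1.293 → 1.268 | 0.305 → 0.430 |
| +7 days | +5.8 | 1.291 → 1.396 | 0.314 → 0.249 |
| −7 days, no true effect on either outcome | −6.9 | 0.998 → 0.907 | 0.984 → 1.303 |

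Share of the log effect lost:

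- Row 1: own mother's milk 1 − ln 1.272 / ln 1.296 = 1 − 0.241 / 0.259 ≈ 7%; NEC 1 − 1.106 / 1.162 ≈ 5%.
- Row 2: own mother's milk 1 − 0.148 / 0.259 ≈ 43%; NEC 1 − 0.821 / 1.149 ≈ 29%.
- Row 3: own mother's milk 1 − 0.237 / 0.257 ≈ 8%; NEC 1 − 0.844 / 1.187 ≈ 29%.

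Check of the formula: row 2 implies β = (0.259 − 0.148) / −8.2 ≈ −0.0134 per day for own mother's milk. Applied to row 4, ln 1.291 + 0.0134 × 5.8 = 0.255 + 0.078 = 0.333, an IRR of 1.40, which agrees with the simulated 1.396.

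Row 5 shows that adjustment can also create an apparent effect where there is none.

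**The case against.** The strongest reply is that length of stay is only an optional example. The default model does not contain it, covariates enter only if characteristics differ, the article expects that they usually will not, and the list is introduced as illustrative. A full analysis plan, not shown, may settle the set. All of this stands, and it limits how often the problem will arise. It does not remove it: the variable is named outright as a potential confounder, and anyone following the text could enter it.

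A second reply is that stay stands in for case mix. The list already covers case mix with gestational age, birth weight and the NMR-2000 score. The first two cannot be altered by care given later in the stay, and the score is equally safe if it uses early-admission data, a timing the article does not state.

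Several stronger readings are tempting, but the article does not support them:

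- **That length of stay is a mediator for every primary outcome.** It may be so in part for feeding at discharge. For day-14 feeding and for NEC it comes later and is at most a consequence.
- **That a bundle which shortens stay necessarily triggers its own adjustment.** The condition, "If the characteristics of infants born during each of the three study time periods differ, we will include covariates", refers to characteristics as a group. A change in stay could set it off, but stay could also enter because something else differs.
- **That stay is cut off for the last births by the end of data collection.** The Time period section sets the three-month follow-up so as to cover the final infant's whole stay, and a monthly median is little affected by a few long stays.
- **That the trigger uses an invalid test.** The sentence "P values for differences between the three time periods will be reported" belongs to the descriptive tables, where a chi-squared or rank-sum test is named. The covariate rule names no test and does not refer to those p values.
- **That a definite loss of effect or power can be stated.** Without length-of-stay figures it cannot.

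**Conclusion.** The concern holds in a limited form. Median length of stay is a post-exposure variable placed in a list of potential confounders for the main ITS model. If it is entered, the IRR is no longer the total effect of the bundle.

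The bias may go either way. It is toward the null if the bundle shortens stay and can go away from it if the bundle lengthens stay, assuming longer stay accompanies less own mother's milk and more NEC. For severe NEC even that assumption is uncertain, because surgery and death may pull stay in opposite directions.

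The size cannot be derived from the article. The illustrations run from a 5–7% loss of the log effect, when stay changes only through feeding and NEC, to 43% (own mother's milk) and 29% (NEC) with an assumed direct shortening of 7 days. These figures rest on the assumed inputs and should not be quoted as expected bias. A reader might infer that adjustment always hides part of a real benefit; the case of lengthened stay and the case of no true effect show otherwise.

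A smaller point also stands. The covariate rule looks for differences across three periods, but only two are modelled. A difference confined to the implementation months could bring in covariates for a contrast it does not affect.

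**What to change.** - Delete median length of stay from the list of potential confounders, and state that only variables fixed at birth or early admission may be added to the ITS model.
- Report length of stay by period and group descriptively, or as an outcome.
- Base the check for differing characteristics on pre-implementation against evaluation, the two modelled periods.

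The cost is one deleted covariate and one reworded sentence. No new data are needed, and case mix stays covered by the remaining variables.
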